## **4.2. Handling of missing data and drop-outs**

The number of missing values for all outcomes for each treatment condition will be reported. There will be no imputation for missing data. For each patient, outcomes calculated from continuously recorded data (e.g. time in sensor glucose ranges) will be calculated if at least 30% of the data of the respective period are available. If less than 30% of data is available, the respective data will be discarded.

# **5 REGULATORY ASPECTS AND SAFETY**

## **5.1 Local regulations / Declaration of Helsinki**

This study is conducted in compliance with the protocol, the current version of the Declaration of Helsinki, the ICH-GCP, the HRA as well as other locally relevant legal and regulatory requirements(1).

## **5.2 (Serious) Adverse Events and notification of safety and protective measures**

An Adverse Event (AE) is any untoward medical occurrence in a patient or a clinical investigation subject which does not necessarily have a causal relationship with the trial procedure. An AE can therefore be any unfavorable or unintended finding, symptom, or disease temporally associated with a trial procedure, whether or not related to it.

A Serious Adverse Event (SAE) (ClinO, Art. 63) is any untoward medical occurrence that

- Results in death or is life-threatening,
- Requires in-patient hospitalization or prolongation of existing hospitalization,
- Results in persistent or significant disability or incapacity, or
- Causes a congenital anomaly or birth defect

Both Investigator and Sponsor-Investigator make a causality assessment of the event to the trial intervention, (see table below based on the terms given in ICH E2A guidelines). Any event assessed as possibly, probably or definitely related is classified as related to the trial intervention.

| Relationship                                                                            | Description                                                                                                               |
|-----------------------------------------------------------------------------------------|---------------------------------------------------------------------------------------------------------------------------|
| Definitely                                                                              | Temporal relationship
Improvement after dechallenge*
Recurrence after rechallenge
(or other proof of drug cause) |
| Probably                                                                                | Temporal relationship
Improvement after dechallenge
No other cause evident                                          |
| Possibly                                                                                | Temporal relationship
Other cause possible                                                                             |
| Unlikely                                                                                | Any assessable reaction that does not fulfil the above conditions                                                         |
| Not related                                                                             | Causal relationship can be ruled out                                                                                      |
| *Improvement after dechallenge only taken into consideration, if applicable to reaction |                                                                                                                           |

Both Investigator and Sponsor-Investigator make a severity assessment of the event as mild, moderate or severe. Mild means the complication is tolerable, moderate means it interferes with daily activities and severe means it renders daily activities impossible.

Device deficiencies (DD) and all **adverse events (AE)** including all **serious adverse events (SAE)** are collected, fully investigated and documented in the eCRF during the entire investigation period, i.e. from patient's informed consent until the last study-specific procedure, including a safety follow-up period (if applicable). Documentation of AEs (including SAEs) by the Sponsor-Investigator, Principal Investigator (or authorized designee) includes diagnosis or symptoms, start and stop dates of event, event treatment, event resolution, assessment of seriousness and causal relationship to the trial intervention.

#### Reporting of SAEs (see ClinO, Art. 63)

All SAEs are documented and reported immediately (within a maximum of 24 hours) to the Sponsor-Investigator of the study.

If it cannot be excluded that the SAE occurring in Switzerland is attributable to the intervention under investigation, the Investigator reports it to the Ethics Committee via BASEC within 15 days.

#### Follow up of (Serious) Adverse Events

The information on (Serious) AEs is systematically collected at the regular visits, as applicable and clinically justified in the context of the specific study setting. Ongoing (serious) Adverse Events will be monitored and documented until event resolution. A standardized follow-up period after study completion or withdrawal, in the absence of study-related safety events, is not deemed necessary, as any untoward, delayed and health-relevant study-related incident are considered unlikely.

#### Notification of safety and protective measures (see ClinO, Art 62, b)

If immediate safety and protective measures have to be taken during the conduct of the study, the investigator notifies the Ethics committee of these measures, and of the circumstances necessitating them, within 7 days.

### 5.3 (Periodic) safety reporting

An annual safety report (ASR) will be submitted once a year to the local Ethics Committee by the Sponsor-Investigator (ClinO, Art. 43 Abs 1).

### 5.4 Pregnancy

Eligibility assessment will not include a pregnancy test as the study intervention (use of a food analysis app) is not contra-indicated during pregnancy and might be even endorsed. However, pregnant women shall be excluded due to concerns regarding data interpretability. To avoid unnecessary burden on the participants, self-reported negative pregnancy status will be considered sufficient. In addition, participants will be encouraged to use a contraceptive method during the time of the study and notify the study team if pregnancy still occurs. Pregnant participant will be withdrawn from the study due to concerns related to data validity.

### 5.5 Amendments

Substantial changes to the study setup and study organization, the protocol and relevant study documents are submitted to the Ethics Committee for approval before implementation. Under emergency circumstances, deviations from the protocol to protect the rights, safety and well-being of human subjects may proceed without prior approval of the Ethics Committee. Such deviations shall be documented and reported to the Ethics Committee as soon as possible.

Substantial amendments are changes that affect the safety, health, rights and obligations of participants, changes in the protocol that affect study objective(s) or central research topic, changes of study site(s) or of study leader and sponsor (ClinO, Art. 29).

A list of all non-substantial amendments will be submitted once a year to the Ethics Committee together with the ASR.

### 5.6 Notification and reporting upon completion, discontinuation or interruption of the study

Upon regular study completion, the Ethics Committee is notified via BASEC within 90 days (ClinO, Art. 38).

The Sponsor-Investigator may terminate the study prematurely according to certain circumstances, e.g.

- Ethical concerns,
- Insufficient participant recruitment,
- When the safety of the participants is doubtful or at risk (e.g. when the benefit-risk assessment is no longer positive),
- Alterations in accepted clinical practice that make the continuation of the study unwise, or
- Early evidence of harm or benefit of the experimental intervention

Upon premature study termination or study interruption, the Ethics Committee is notified via BASEC within 15 days (ClinO, Art. 38).

All health-related data will be stored for a total of 10 years after study termination or premature termination of the study.

A final report is submitted to the Ethics Committee via BASEC within a year after completion or discontinuation of the study, unless a longer period is specified in the protocol (ClinO, Art. 38).

### 5.7 Insurance

The present study represents a risk Category A1 investigation and is therefore exempt from study insurance policies (Art. 3 ClinO-MD).

## **6 FURTHER ASPECTS**

### **6.1 Overall ethical considerations**

Approval of the lead Ethics Committee will be obtained before the commencement of any study-related activities. Additional requirements set by the authorities will be implemented throughout the study.

The study procedures do not expose participants to any additional risk or invasive procedures. Apart from using the SNAQ app and undergoing the planned remote or in-person visits, participation in the trial does not impose additional burden on the patients. Meal management apps are widely used in the population. The SNAQ app has been on the market for several years and currently counts more than 40,000 users (with over 2,500 users in Switzerland).

Although real life data from an observation study involving people with type 1 diabetes were presented at the Diabetes Technology Meeting 2021, we are not aware of any randomized clinical trial assessing the benefits of SNAQ app on various aspects of type 1 diabetes people's live (e.g. glucose control, satisfaction with the app, food literacy, etc.). Given the wide-spread use of SNAQ app in the diabetes community and several endorsements of the app on digital media, we feel that an objective assessment through the use of a proper study design and statistical techniques, conducted by a purely academic research team without any conflicts of interest, could provide people with type 1 diabetes with a better basis for decision-making of meal management tools such as SNAQ app. This necessity was also perceived by patient public involvement contributors.

### **6.2 Risk-benefit assessment**

One of the most challenging aspects of managing type 1 diabetes is meal planning and assessment, in particular carbohydrate counting, which takes up a lot of time and efforts in people's daily life. Although nutritional values (e.g. carbohydrate content per standard serving) can be accessed by various tools (e.g. libraries, exchange tables), estimation of portion sizes often relies on the people's visual estimation as weighing food is often not a viable or convenient option in daily life. Outcomes of patient survey suggest that carbohydrate counting significantly contributes to the burden of type 1 diabetes self-management and that there is a general hope that new technology could lower it. By using SNAQ app, participants are provided with a simple method that may aid them to estimate carbohydrate contents with greater accuracy and hence improve postprandial control. Apart from the potentially positive influence of the food analysis app on glucose control and burden of self-management, the app has the potential to enhance participants' capacity to access nutritional information, increase health- and nutrition-related knowledge as well skills in preparing well-balanced meals of high nutritional quality. Increased food literacy and self-efficacy is an established predictor for the prevention of cardiovascular complications.

In terms of risk, previous work suggest that the SNAQ app estimates food carbohydrate content with greater accuracy than the average patient [9]. In addition, the food analysis app, SNAQ, only supports the estimation of carbohydrate content, but the final decision in terms of treatment decisions lies with the participants. As a consequence, the use of the app is by no means related to higher risk than when counting carbohydrate by experience or other methods of choice. We therefore interpret the risk-benefit-ratio in favour of the benefits.

## **7 QUALITY CONTROL AND DATA PROTECTION**

### **7.1 Quality measures**

For quality assurance the sponsor, the Ethics Committee or an independent trial monitor may visit the research sites. Direct access to the source data and all study related files is granted on such occasions. All involved parties keep the participant data strictly confidential. Study personnel will be trained on all important study related aspects. Quality measures will follow the standardized

procedures of the University Clinic for Diabetes, Endocrinology, Nutritional Medicine and Metabolism which include an internal review of the procedures and a check to the adherence to good clinical practice guidelines. An independent data review by a trained data manager will be performed and all data will be checked for plausibility.

## **7.2 Data recording and source data**

All study data will be collected in an electronic Case Report Form (eCRFs) or downloaded directly from the devices. Data from the participants' usual care hybrid closed-loop systems will be de-identified and coded with the Study ID. The imported data from the SNAQ app is already de-identified because they will be logged-in with their study ID. All data will be archived in a coded format in the study database RedCap with the exception of signed informed consent forms which will be stored in a locked cabinet.

During the study, eCRFs will be maintained and kept current by the study team. eCRFs are linked with participants' study ID. The study delegation log describes who will be authorized for eCRF entries and access to the data. Once data collection is completed and validated, the Sponsor-Investigator will sign off all eCRFs. The Sponsor-investigator is responsible for the correctness of the entered data and confirms this by means of the electronic signature in the RedCap database. The data management plan specifies what constitutes source data. In case eCRFs are not serving as source documents, source documents will be retained for audit trail purposes. Location of source data is specified in the data management plan.

Source documents in this trial entail the following:

- Signed and dated informed consent forms
- Randomisation logs
- Insulin and CGM data exported from the closed-loop systems (via the proprietary platforms such as Glooko or Carelink)
- Meal macronutrient contents and timing exported from the SNAQ app.
- eCRFs on which data are entered directly

Any change or correction to source data will be dated, marked with staff initials, and explained (if necessary) and should not obscure the original entry.

All data captured in the eCRF will be itemised on a source data location list, which will be stored in the investigator site file. This list should clearly indicate the source data location corresponding to each eCRF entry. If several sources are possible for one eCRF entry, the priority order of these will be specified in the list. If certain data are directly entered into the eCRF (and are thus considered as source data) this will be specified on the location list accordingly.

*Note: If the participants send the data without de-identifying them beforehand, the study team will de-identify data before uploading the data in REDCap.*

## **7.3 Confidentiality and coding**

Trial and participant data will be handled with uttermost discretion and is only accessible to authorised personnel who require the data to fulfil their duties within the scope of the study. On the CRFs and other study specific documents, participants are only identified by a unique study ID.

All collected data will be labelled with the subject ID (composed of the study acronym and a two digit number; e.g. SuMMIT\_01). No biological specimens will be collected. The subject identification list will be kept in the Investigator Site File during the course of the clinical trial. During the study the Sponsor-Investigator has access to all documents of the investigation including randomization lists and coding keys.

After completion or termination of the study, the subject identification list will be kept by a person outside of the study team ([name], Department of Diabetes, Endocrinology Nutritional Medicine and Metabolism, University Hospital Bern). In case of further use of research data, the researchers in charge will not have access to the subject identification list.

Direct access to source documents will be permitted for purposes of monitoring, audits and inspections. The Sponsor-Investigator will declare who will have access to the documents of the investigation, dataset, randomization code, etc. during and after the investigation.

The study data base in REDCap® can only be accessed by designated investigator staff entering a username and password. The application has a group and role-based security model. Each user belongs to one or more security groups with specific sets of permissions about folder or projects in the system. Only dedicated site administrators have access to the admin console, enabling user management and changing security settings.

All events are recorded in the user event list of the audit log files. Data are stored and visualised in data grids either in the format of datasets, lists or assays. Each change of data is tracked and documented in corresponding audit log files.

The servers are behind a firewall and cannot be accessed through the internet. They are located in locked dedicated server rooms with restricted access. Apache HTTP Server and REDCap® were configured to run under Secure Sockets Layer (SSL) which implies that data is encrypted and transmitted securely.

Available disk space is monitored actively. If free disk space is less than 10%, administrators get an email, and more storage capacity will be added accordingly.

All servers are regularly backed up on storage servers in a separate server room using a multi-level system.

#### **7.4 Retention of study data**

Paper-based trial documents (e.g. Informed Consent) will be adequately stored within the facilities of the Department of Diabetes, Endocrinology, Nutritional Medicine and Metabolism for at least 10 years after completion of the study. The study database will be securely stored at Department of Diabetes, Endocrinology, Nutritional Medicine and Metabolism, Inselspital, Bern and the retention duration of study documents will follow local legal requirements.

If subjects provided consent for the further use of their data (independently of the investigation specific consent), data will be stored in the same database for an undetermined length of time and will be accessible for reuse in the context of other research projects. No biological samples will be collected.

### **8 MONITORING AND REGISTRATION**

The Sponsor-Investigator will ensure oversight of the clinical research study by means of pre-defined monitoring visits. The level and type of monitoring will be commensurate with the Swiss Clinical Trial organization SCTO Risk Monitoring Score of 2 corresponding to a low risk. Source data and all project related files and documents will be made accessible to monitors. The Sponsor-Investigator and site staff will be available and ready to answer questions that may arise during the monitoring. Details will be specified in a dedicated monitoring plan.

The study will be registered in the Swiss National Clinical trial Portal (SNCTP via BASEC). In addition, the study will be registered in clinicaltrials.gov, a registry listed in the WHO International Clinical Trials Registry Platform.

## **9. FUNDING / PUBLICATION / DECLARATION OF INTEREST**

The project was granted seed funding from the European Foundation for the Study of Diabetes (EFSD, call on Digital Diabetes).

Study findings will be disseminated to study participants, healthcare professionals, the public, and scientist via summaries in lay language, scientific presentations and peer-reviewed publications. The privacy of each subject and confidentiality of their information shall be preserved in reports and publication of data. Disseminations will be detailed in a publication plan. If sex or gender effects are observed, they will be published in the final study report. Once results have been published, trial data will be accessible to external researchers. Investigators wishing to replicate the analyses or to do an individual patient meta-analysis may request the data from the Sponsor-Investigator. The investigators do not declare any conflict of interest.

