#### **Pre-defined exploratory endpoints:**

*The following endpoints will be examined to assess various aspects of SNAQ app use in terms of usefulness, nutrition literacy, psychosocial, and behavioral impact. Pre-specified exploratory endpoints will be reported as point estimates with 95% confidence intervals (unadjusted for multiple testing), so definite inferences cannot be made regarding those endpoints.*

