# **4 STATISTICS AND METHODOLOGY**

## **4.1. Statistical analysis plan and sample size calculation**

### *Sample Size calculation*

Sample size was estimated to provide sufficient power to detect a clinically meaningful difference of 10% in the primary efficacy outcome. The sample size was calculated based on preliminary data on the efficacy of SNAQ app in improving postprandial glucose control. In data from 23 subjects (1603 meals with SNAQ app and 2018 meals without SNAQ app), mean $\pm$ SD time in target range was 85 $\pm$ 23% vs. 77 $\pm$ 35% with and without the app, respectively. Assuming a mean improvement of 10% in the intervention group with no change in the control group, and assuming

a within-participant standard deviation of 10% in both groups, a total sample size of 34 participants (17 per group) is required to achieve a power of 80% at a two-sided alpha level of 5%. Assuming a drop-out rate of 20%, we therefore aim to recruit 44 participants (22 per group).

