#### *Statistical analysis*

For the efficacy analysis, outcomes will be compared between the two groups using general linear models (GLM). All endpoints evaluating the efficacy of the intervention (main analysis) will be adjusted for their values at baseline. For the sustainability analysis, baseline data and the 3 weeks following SNAQ app discontinuation will be compared using pooled data from both groups. GLM techniques considering the paired data structure will be used. In case of non-normality of the residuals, data will be transformed appropriately. All analyses will be performed using all available data (see section 4.2 for handling of missing data). P-values below 5% will be considered statistically significant. Exploratory endpoints will be reported as point estimates with 95% confidence intervals (unadjusted for multiple testing), so definite inferences cannot be made regarding those endpoints.

Statistical analysis will be performed using the software R and/or Stata. A detailed statistical analysis plan will be written before the start of the study.

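### Section 9 makes publication of sex or gender effects depend on the result; the estimates should be reported whatever they show (minor)

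*Protocol*

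**What the plan says.** Section 9 of the protocol (funding, publication, declaration of interest) states: "If sex or gender effects are observed, they will be published in the final study report". It names no endpoint or analysis, does not say what counts as an observed effect, and does not say what happens if none is seen.

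Sex or gender otherwise appears in two places. Sex is one of three minimisation factors in section 3.5, and gender is a baseline variable in section 3.3. Section 4.1 describes no sex analysis, but announces a detailed statistical analysis plan, which is not available here.

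For the exploratory endpoints in section 2.1 the protocol takes a different line: "Pre-specified exploratory endpoints will be reported as point estimates with 95% confidence intervals (unadjusted for multiple testing), so definite inferences cannot be made regarding those" (that is, the outcomes listed there). That commitment does not depend on what the estimates show. Sex effects are not in the list it covers.

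**The concern.** A reporting rule triggered by the result is a selection rule. Whatever definition of an observed effect is used, large estimates pass and small ones need not be shown. In a large trial this does limited harm, because large estimates are mostly real. In a trial of 34 to 44 people an interaction estimate is mostly noise. One that looks striking is likely to be far from the truth, and an unremarkable one may never reach the reader.

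What is at stake is a secondary message of the report: whether the app appears to help one sex more than the other. The sentence is a positive statement in the protocol. A later analysis plan could define the model, but the written publication commitment would stay conditional unless section 9 is changed.

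**Working it through.** **Inputs from section 4.1 of the protocol**
- Effect: "Assuming a mean improvement of 10% in the intervention group with no change in the control group".
- SD: "a within-participant standard deviation of 10% in both groups", used here as the SD of the outcome in each arm, which is how the protocol's sample size is reproduced.
- Two-sided alpha 5%, power 80%; 34 evaluable (17 per group); 20% drop-out; 44 recruited (22 per group).

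**Assumptions not in the protocol**
- Half the participants are women; a 30:70 split is shown as a range.
- The SD is the same in both sexes.
- Residual degrees of freedom are N − 4.

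**Step 1: reproduce the protocol's figure.** For a two-sample t-test with difference 10 and SD 10, power from the noncentral t is 78.1% with 16 per arm and 80.7% with 17 per arm. So 17 per arm, 34 in total. Drop-out: 17 / (1 − 0.20) = 21.25, rounded up to 22 per arm, 44 in total. Both figures agree with the protocol.

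**Step 2: precision of the sex interaction.** With n_F women and n_M men per arm:

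SE(effect within one sex) = 10 × √(2/n)

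SE(interaction) = 10 × √(2/n_F + 2/n_M)

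- N = 34, half women: 8.5 of each sex per arm. Within-sex SE = 10 × √(2/8.5) = 4.85. Interaction SE = 10 × √(4/8.5) = 6.86.
- N = 44, half women: 11 of each sex per arm. Within-sex SE = 10 × √(2/11) = 4.26. Interaction SE = 10 × √(4/11) = 6.03.

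As a check, the SE of the main effect with 17 per arm is 10 × √(2/17) = 3.43. With an even split the interaction SE is twice that, 6.86. This ratio of two holds whatever the SD.

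**Step 3: what a filter would let through.** The protocol does not say what *observed* means. To illustrate, take one possible filter: a two-sided 5% t-test of the interaction on the primary endpoint. The smallest significant estimate is about t(0.975, N − 4) × SE: 2.042 × 6.86 = 14.0 points, or 2.021 × 6.03 = 12.2 points. Power is from the noncentral t.

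| Evaluable N | Share of one sex | Interaction SE | Smallest significant estimate | Power, true 5 points | Power, true 10 points |
|---|---|---|---|---|---|
| 34 | 50% | 6.9 | 14.0 | 11% | 29% |
| 34 | 30% | 7.5 | 15.3 | 10% | 25% |
| 44 | 50% | 6.0 | 12.2 | 13% | 37% |
| 44 | 30% | 6.6 | 13.3 | 12% | 32% |

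**Step 4: exaggeration.** In a simulation of this t-test with an even split and a true interaction of 5 points, the estimates that reach p < 0.05 average 16.4 points in absolute size with N = 34 and 14.7 with N = 44. That is about three times the truth (16.4 / 5 = 3.3; 14.7 / 5 = 2.9). With N = 34 the average is about 16 to 18 points whether the true difference is 0, 5 or 10, so an estimate that passes says little about the true value.

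**The case against.** The strongest reply is that section 9 is a dissemination statement, not an analysis rule. It promises to publish effects that are seen and does not forbid publishing others. The model, endpoint and exploratory label may be in the analysis plan, and section 9 also announces a publication plan. All of this stands. The absence of a test or label in the protocol is not part of this point. The conditional wording is.

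A reader might infer more than the documents support, in four ways.

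- **That sex effects are published only if significant at 5%.** Section 4.1 says "P-values below 5% will be considered statistically significant", but nothing ties that sentence to sex effects, and section 9 does not say *only*. The 5% filter above is an illustration.
- **That null results will be left out and chance differences reported as findings.** The text is silent on null results. Both outcomes are possible, and neither is stated.
- **That all twelve primary and secondary endpoints form a family of sex tests with a much inflated false-positive rate.** The protocol names no sex test on any endpoint. Endpoints 1 to 3 divide the same time and sum to 100%, as do 4 to 6, so calculations that treat them as independent do not apply. Endpoints 7 to 12 are analysed in section 4.1 as paired comparisons pooled over both groups, where a treatment-by-sex interaction of the kind computed here is not defined. For a single 5% test on the primary endpoint the chance-positive rate is 5%.
- **That others could not pool the sex-specific results.** Section 9 offers the trial data on request, including for individual patient meta-analysis.

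**Conclusion.** The point holds as a minor one. Section 9 makes publication of sex or gender effects conditional on their being seen, with no commitment otherwise. At this trial's size that condition may select chance or exaggerated differences. The interaction SE is about 6.9 points with 34 evaluable participants and 6.0 with 44, and power for a true 5-point difference is 11% and 13%. Even a difference of 10 points, as large as the whole effect the trial is sized for, would be detected only 25% to 37% of the time over the scenarios shown.

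These figures rest on the protocol's SD of 10 points, an equal SD in both sexes, and an assumed sex split of 50:50 or 30:70. A smaller residual SD after baseline adjustment would shrink the standard errors in proportion, but with an even split the interaction would still be half as precise as the main effect. No figure in the protocol is wrong on this point, and the primary analysis and sample size are unaffected.

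**What to change.** Replace the sentence in section 9 with, for example:

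*The treatment-by-sex interaction for the primary endpoint and the effect within each sex will be reported as point estimates with 95% confidence intervals whatever the result, as exploratory; any sex effects examined on other endpoints will all be reported in the same way.*

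The analysis plan should carry a matching line. This brings sex effects into line with how section 2.1 already treats the exploratory endpoints.

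The cost is one sentence and one additional model. No new data are needed, because sex is already collected for the minimisation. The downside is that an imprecise estimate must be published even when it tells the reader little: under the assumptions above with an even split, the 95% interval for the interaction would be about ±14 points with 34 evaluable participants and ±12 points with 44.
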